#### MRI scan

2.10.3

For participants who volunteer for the magnetic resonance imaging (MRI) brain scan, MRI compatibility is determined through screening questions for contraindications, including implanted medical devices and recent surgeries. Eligible participants then complete a brain MRI scan at baseline and again at end-of-trial. Scanning sequences are from the Human Connectome Project Development and Aging protocol (HCP D/A; Harms et al., 2018). These protocols are commonly used within human neuroimaging, and provide high temporal and structural resolution (Glasser et al., 2016). Specific scans run include functional MRI (fMRI; task-based and resting-state), diffusion-weighted imaging, and T1- and T2-weighted structural scans. Details of MRI sequences and task paradigms are provided below.

##### Structural scans—T1 & T2

2.10.3.1

A high-resolution T1-weighted volume is acquired at baseline using an MPRAGE sequence with volumetric navigators (vNav) for prospective motion correction: TR = 2,500 ms, TE = 1.81 ms, TI = 1,000 ms, flip angle = 8 °, in-plane GRAPPA acceleration factor = 2, 0.8 mm isotropic voxels, matrix = 320 × 298, 208 sagittal slices, duration = 8 min 22 s. Four echoes are acquired and combined as a root-mean-square (RMS) image to enhance SNR. A matched T2-weighted volume is acquired at end of trial using a SPACE sequence with vNavs: TR = 3,200 ms, TE = 564 ms, variable flip angle (peak 120 °), in-plane GRAPPA acceleration factor = 2, 0.8 mm isotropic voxels, matrix = 320 × 300, duration = 6 min 35 s.

##### FMRI parameters

2.10.3.2

Functional data are acquired using a multiband gradient-echo EPI sequence: TR = 800 ms, TE = 37 ms, flip angle = 52 °, multiband acceleration factor = 8, 2 mm isotropic voxels, matrix = 104 × 104, effective echo spacing = 0.58 ms, total readout time = 59.7 ms. Eight BOLD runs are acquired per participant. Two stop signal and two interoception task runs are collected (one of each per session, with phase encoding in the posterior-anterior direction). Four resting-state runs are collected (two per session) with alternating phase encoding (anterior-posterior and posterior-anterior) to enable distortion correction. Spin-echo field map pairs with opposing phase-encoding directions (AP and PA) are acquired adjacent to each set of functional runs to support EPI distortion correction: TR = 8,000 ms, TE = 66 ms, flip = 90 °, identical EPI geometry to the BOLD runs. A single band reference image is collected prior to the start of each fMRI run.

##### FMRI—stop signal task

2.10.3.3

The stop-signal task consists of a single run, with a possible maximum of 750 volumes over 10 min. 240 trials are presented in total, including 180 “go” and 60 “stop,” presented in a fully randomized order. In each trial (Figure 3), participants are presented with an arrow pointing either left or right. Participants are encouraged to respond by pressing a button as quickly and as accurately as possible using a button box in their right hand (left arrow = index finger, right arrow = middle finger). On “stop” trials, after a short variable delay, the presented arrow turns red and an audio cue (1,000 Hz, 100 ms) sounds, indicating that the participant should withhold the button press.

**Figure 3 F3:**
[figure not shown]
Procedure for the functional magnetic resonance imaging stop signal task. On “go” trials, a black arrow pointing left or right is presented for 1,000 ms, and participants indicate arrow direction using a button response. On “stop” trials, a “go” black arrow is initially presented and then replaced by a red arrow alongside an audio tone after a variable stop signal delay. Trials are preceded by a fixation cross of variable duration.

Go trials have a set duration of 1,000 ms. For the first stop trial, a stop signal delay (SSD) of 250 ms is used. Over subsequent stop trials, this value adaptively responds to a participant's performance, such that SSD decreases by 50 ms if the previous response was correctly withheld, and increases by 50 ms if not. This adaptive design helps to ensure that approximately 50% of stop trials are classified as successful and 50% as unsuccessful. This is important for subsequent calculation of the stop signal response time (SSRT), which rests on assumptions of the independent race model. This model assumes that a stop signal task constitutes an independent race between a “go runner” and a “stop runner” (Verbruggen et al., 2019). Participants employing deliberate strategies, in which anticipation of stop signals interferes with response time on go trials, can violate this assumption of independence, and undermine the adaptive modulation of SSD duration. As such, participants are explicitly instructed not to wait to see if the presented arrow turns red before responding, but to prioritize responding quickly and accurately to the arrow direction, and try to stop if the stop cue appears. Trials are separated by a fixation cross intertrial interval, with a variable duration of 1,000 ms (35%), 1,130 ms (30%), 1,250 ms (20%), 1,380 ms (10%), or 1,500 ms (5%). The design of this task was guided by best practice recommendations from Verbruggen et al. (2019).

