##### FMRI—interoception task

2.10.3.4

The interoception task was adapted from the “Visceral interoceptive awareness task” described by Livermore et al. (2024). This task consists of one run, with a possible maximum of 1,125 volumes over 15 min. During this task, participants are presented with three trial types (Figure 4), two interoceptive and one exteroceptive:

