**Figure 4 F4:**
[figure not shown]
Procedure for functional magnetic resonance imaging interoception task. Stimuli are split according to trial type, including the interoceptive conditions of “heart” and “stomach” and the exteroceptive control condition of “target.” Stages of each trial are presented, including the “get ready” cue (2 s), the focus period (10 s), and the intensity rating period (up to 4 s).

**Heart**: Participants are instructed to focus on the internal sensation of their heart.**Stomach**: Participants are instructed to focus on the internal sensation of their stomach.**Target**: Participants are instructed to attend to the word “Target,” which repeatedly changes color from black to a shade of gray with varying degrees of intensity, for a randomly selected duration between 0.7 and 1.1 s.

Following interoceptive and exteroceptive trials, participants rated the intensity of the internal sensations (HEART, STOMACH) or of the color change (TARGET), respectively, on a scale from 1 (“not at all”) to 4 (“very”).

Each session contains 48 trials (16 Heart, 16 Stomach, 16 Target). Each trial is preceded by a “get ready” instruction lasting 2 s. During each rating period, participants provide a response using a button box in their right hand (1 = index finger, 2 = middle finger, 3 = ring finger, 4 = little finger). Rating scales are presented (and responses logged) for a maximum of 4 s. If a response is provided before the end of this period, the prompt remains on screen for another 0.5 s before proceeding. The exact total length of the task is therefore variable across participants. Each rating period is followed by a fixation cross of a variable duration: 3 s (10.42%), 4 s (12.50%), 5 s (18.75%), 6 s (25.00%), 7 s (20.83%), 8 s (8.33%), 9 s (2.08%), 11 s (2.08%).

The task is identical to that used in (Livermore et al. 2024), except that intensity ratings are collected after every trial (rather than only on some trials in Livermore et al., 2024). Participants completed one of two fixed trial order sets in each session, with set order counterbalanced between participants.

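### The stop-signal staircase is written with its sign reversed, so as specified it cannot give 50% stopping, and the interoception run cap is shorter than the task it must hold

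*Protocol article*

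**What the plan says.** **Stop-signal task (Section 2.10.3.3).** On trial numbers: "240 trials are presented in total, including 180" go trials and 60 stop trials. On the starting point: "For the first stop trial, a stop signal delay (SSD) of 250 ms is used". On later stop trials: "SSD decreases by 50 ms if the previous response was correctly withheld, and increases by 50 ms if not". The stated aim follows directly: "This adaptive design helps to ensure that approximately 50% of stop trials are classified as successful and 50% as unsuccessful". The reason is also given: "This is important for subsequent calculation of the stop signal response time (SSRT), which rests on assumptions of the independent race model".

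**Interoception task (Section 2.10.3.4).** On run length: "This task consists of one run, with a possible maximum of 1,125 volumes over 15 min". Each session has 48 trials. Each trial has a 2 s cue, a 10 s focus period, a rating period and a fixation cross of 3 to 11 s with stated percentages. On the rating: "Rating scales are presented (and responses logged) for a maximum of 4 s"; after an earlier response the prompt stays for a further 0.5 s. The section adds that total task length varies between participants. Section 2.10.3.2 gives a repetition time of 800 ms.

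**The concern.** In the race model that the article invokes, the SSD is the head start given to the go process. Shortening it makes stopping easier and lengthening it makes stopping harder. The written rule therefore makes the task easier after a success and harder after a failure. That is positive feedback, and it cannot hold stopping near 50%. The rule and its stated aim stand next to each other and contradict each other.

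If the code follows the text, nearly all of a participant's 60 stop trials have the same outcome. SSRT is then unreliable or undefined, and the contrast of successful with failed stops has almost nothing on one side. Section 1.1.6 names this task as the measure of change in prefrontal function.

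The interoception cap is a second, separate contradiction in the same part of the protocol. If acquisition stops at the cap, trials at the end of each fixed-order set go unrecorded, and slower raters lose more of them.

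Scanning has been under way since 2022 and is due to finish in 2027 (Section 2.6), so an error in the code would affect data already collected as well as data to come. Section 4 also offers the protocol as a model for other researchers, who could copy the rule.

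**Working it through.** **1. Direction of the staircase**

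Under the independent race model a stop succeeds when go RT > SSD + SSRT. So p(success) falls as SSD rises.

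- As written: expected change in SSD per stop trial = −50p + 50(1 − p) = 50(1 − 2p) ms. If p > 0.5, SSD falls and p rises further. If p < 0.5, SSD rises and p falls further. The 50% point is unstable.
- Sign reversed: expected change = 50(2p − 1) ms. Any departure from p = 0.5 is pulled back.

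The sign alone settles the contradiction. Simulation only sizes it.

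**2. Size of the effect**

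From the article: 60 stop trials, starting SSD 250 ms, step 50 ms, and a go trial of 1,000 ms (a later go response counts as withheld). Assumed, because the article gives no values: ex-Gaussian go RT, mean SSRT of 200 to 250 ms with SD 30 ms, and SSD kept between 0 and 1,000 ms. There were 2,000 sessions per row and rule.

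| Mean go RT / SSRT (ms) | As written: >90% stops | As written: <10% stops | As written: 25–75% | Reversed: mean stopping | Reversed: 40–60% |
|---|---|---|---|---|---|
| 430 / 200 | 26.2% | 73.4% | 0% | 49.5% | 100% |
| 500 / 220 | 61.0% | 37.8% | 0% | 50.2% | 100% |
| 550 / 220 | 89.4% | 9.9% | 0% | 51.1% | 100% |
| 600 / 250 | 94.4% | 5.4% | 0% | 51.5% | 100% |
| 650 / 220 | 99.9% | 0.1% | 0% | 52.8% | 100% |

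As written, the two extremes together hold 98.8% (61.0 + 37.8) to 100% of sessions. A separate run of 4,000 sessions (go RT 500 ± 90 ms, SSRT 220 ms) gave 99.7% at or beyond 10% or 90%. Four further assumed settings gave 96% to 100%. In both of these checks no session fell between 40% and 60%. The stated 50% is reproduced only with the sign reversed.

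At 10% or 90%, one side of the contrast has at most 0.10 × 60 = 6 trials. The direction of the collapse also depends on go speed, so a change in go speed between visits could look like a change in stopping.

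**3. Interoception run length**

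- Stated cap: 1,125 × 0.8 s = 900 s, which agrees with the stated 15 min.
- Cue and focus: 48 × (2 + 10) = 576 s.
- Fixation: the stated percentages are 5, 6, 9, 12, 10, 4, 1 and 1 of 48 trials at 3, 4, 5, 6, 7, 8, 9 and 11 s. Total: 15 + 24 + 45 + 72 + 70 + 32 + 9 + 11 = 278 s.
- Before any rating: 576 + 278 = 854 s.
- Left for ratings: (900 − 854)/48 = 0.96 s each. Less the 0.5 s hold, that allows a mean response time of about 0.46 s.

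| Mean rating period | Run length | Over the cap | Trials lost at the cap |
|---|---|---|---|
| 1 s | 902 s | 2 s | 2/(902/48) = 0.1 |
| 2 s | 950 s | 50 s | 50/(950/48) = 2.5 |
| 4 s (stated maximum) | 1,046 s | 146 s | 146/(1,046/48) = 6.7 |

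The maximum is 1,046/0.8 = 1,307.5, so 1,308 volumes.

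**4. Comparison with the stop-signal run**

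The mean inter-trial interval from the stated percentages is 1.152 s. Run length is 240 × (1.0 + 1.152) = 516 s, within its cap of 750 × 0.8 = 600 s. The same arithmetic raises no problem there.

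**The case against.** **It may be only a wording slip.** Section 2.10.3.3 states the right aim, explains why SSRT needs it, tells participants not to wait for the signal, and cites best-practice guidance. After years of scanning, a correct script with a reversed sentence is at least as plausible as a wrong script. This stands: the article cannot tell the two apart, so the loss of SSRT is conditional on the code. The contradiction in the text does not depend on it.

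**The reach is limited.** MRI is optional, the task is one of several sequences, and the sample size rests on questionnaires. Go-trial data would survive. This stands too, but the task is the named test of response inhibition.

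**The interoception cap may be a misstated maximum, not a cut-off.** Nothing says that runs stop at 900 s, so truncation is an inference. If only the last fixation were lost, the threshold would rise to about (46 + 5.79)/48 = 1.08 s. The loss is modest at a 2 s rating period, and set order is counterbalanced between participants. All fair, but the stated maximum is still exceeded. Counting the cue inside the focus period, which the text does not support, still gives 48 × 14 + 278 = 950 s.

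**Lengthening the run now could track group.** Apart from one employer in 2022, controls date from 2025, so a mid-study change could align acquisition length with group or split one person's two scans. This is a real caution, and the fix takes account of it.

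**Conclusion.** Both contradictions hold on the article's own text. The staircase as written drives stopping towards 0% or 100% and cannot give the stated 50%. That follows from the sign alone; the size (96% to 100% of sessions at the extremes) rests on assumed RT and SSRT values but was stable across every setting tried. If the code matches the text, SSRT and the stop contrast cannot be used. If it does not, the published method is wrong and needs correcting.

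The interoception maximum is understated by up to 146 s (183 volumes), and the run fits only if rating periods average under 0.96 s. This uses stated timings only. Whether any run was actually truncated is not known from the article.

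**What to change.** 1. Check the stop-signal script and the logged SSDs now. In every session, confirm that SSD rose after a successful stop and fell after a failed one, and tabulate the stopping rate.
2. Correct Section 2.10.3.3 so that SSD increases by 50 ms after a correctly withheld response and decreases by 50 ms after a failed one. The text needs this whatever the check shows.
3. If any sessions ran as written, exclude their SSRT and stop contrasts, and report the number by group and visit.
4. Count interoception runs that ended before the last trial, by group and visit, and report this.
5. Reconcile Section 2.10.3.4. Either state a run length of at least 1,308 volumes (17 min 26 s) or say that acquisition ends on task completion. If acquisition changes mid-study, record the date, avoid splitting a participant's two visits across it where possible, and allow for it in the analysis, since most controls are scanned later than much of the intervention group.

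The cost is a check of code and logs and two text corrections. If the run is lengthened, it adds up to 146 s (about 2.5 min) of scanning per session.

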##### FMRI—interoception task

2.10.3.4

The interoception task was adapted from the “Visceral interoceptive awareness task” described by Livermore et al. (2024). This task consists of one run, with a possible maximum of 1,125 volumes over 15 min. During this task, participants are presented with three trial types (Figure 4), two interoceptive and one exteroceptive:

**Figure 4 F4:**
[figure not shown]
Procedure for functional magnetic resonance imaging interoception task. Stimuli are split according to trial type, including the interoceptive conditions of “heart” and “stomach” and the exteroceptive control condition of “target.” Stages of each trial are presented, including the “get ready” cue (2 s), the focus period (10 s), and the intensity rating period (up to 4 s).

**Heart**: Participants are instructed to focus on the internal sensation of their heart.**Stomach**: Participants are instructed to focus on the internal sensation of their stomach.**Target**: Participants are instructed to attend to the word “Target,” which repeatedly changes color from black to a shade of gray with varying degrees of intensity, for a randomly selected duration between 0.7 and 1.1 s.

Following interoceptive and exteroceptive trials, participants rated the intensity of the internal sensations (HEART, STOMACH) or of the color change (TARGET), respectively, on a scale from 1 (“not at all”) to 4 (“very”).

Each session contains 48 trials (16 Heart, 16 Stomach, 16 Target). Each trial is preceded by a “get ready” instruction lasting 2 s. During each rating period, participants provide a response using a button box in their right hand (1 = index finger, 2 = middle finger, 3 = ring finger, 4 = little finger). Rating scales are presented (and responses logged) for a maximum of 4 s. If a response is provided before the end of this period, the prompt remains on screen for another 0.5 s before proceeding. The exact total length of the task is therefore variable across participants. Each rating period is followed by a fixation cross of a variable duration: 3 s (10.42%), 4 s (12.50%), 5 s (18.75%), 6 s (25.00%), 7 s (20.83%), 8 s (8.33%), 9 s (2.08%), 11 s (2.08%).

The task is identical to that used in (Livermore et al. 2024), except that intensity ratings are collected after every trial (rather than only on some trials in Livermore et al., 2024). Participants completed one of two fixed trial order sets in each session, with set order counterbalanced between participants.

##### FMRI—resting-state

2.10.3.5

Resting-state fMRI is acquired in both AP and PA directions (2 runs total), with preceding spin echo field maps and identical BOLD acquisition parameters to the task-based parameters. Each run contains 565 volumes (7 min 53 s), for a combined total of 1,130 volumes (15 min 46 s). During these scans, participants are instructed to keep their eyes open and focus on a white fixation cross presented a black background.

##### Diffusion-weighted imaging

2.10.3.6

Diffusion-weighted imaging is conducted across two runs (AP/PA), each with a scan time of 5 min 42 s per run (11 min 24 s total). Images are acquired using a multiband EPI sequence: TR = 3,230 ms, TE = 89.2 ms, flip angle = 78 °, multiband acceleration factor = 4, 1.5 mm isotropic voxels, matrix = 140 × 140, 92 axial slices, effective echo spacing = 0.69 ms, total readout time = 95.9 ms. Two diffusion shells are acquired (*b* = 1,500 and *b* = 3,000 s/mm^2^) with 47 and 46 directions per shell, respectively, per acquisition, plus 7 interleaved *b* = 0 volumes. Each shell direction set is acquired twice, once with anterior-posterior and once with posterior-anterior phase encoding, to enable distortion correction. A complementary 98-direction acquisition with the same shell structure is also collected in both phase-encoding directions, yielding a total of 197 unique diffusion-weighted directions per shell pair across the two acquisitions. Directions per shell are halved relative to the HCP standard sequence to reduce overall scan time.

Further details on all sequences are provided in the *Human Connectome Imaging protocols for the Lifespan Development and Aging* projects (Harms et al., 2018). All data are preprocessed using the HCP minimal preprocessing pipelines (Glasser et al., 2013) as implemented in QuNex 1.4.3 (Ji et al., 2023), with additional ICA-FIX denoising and MSMAll multi-modal areal-feature-based surface registration. Further details of which will be provided in the subsequent MRI-specific preregistration for this project.

For the duration of all MRI scan sequences, participants are equipped with a pulse oximeter (by default, on the index finger of their left hand). This allows for measurement and analysis of heart rate variability. This will enable deeper understanding of any changes observed on the interoception attention task, as changes in heart rate variability after working time reduction may be associated with changes in neural processes of interoceptive attention. Prior research suggests an association between interoceptive accuracy for heartbeat monitoring and heart rate variability (Lischke et al., 2021; Saito et al., 2025).

## Statistical analysis

3

The primary objective of this research project is to understand how health, wellbeing, and work performance measures change following a reduction in working time, compared with a control group. The secondary objective will be to investigate whether individual differences, including variables such as sex, age, extent of working time reduction, and baseline score for a given measure, moderate these effects. In Sections 2.7–2.10, we summarized all data to be collected. The overall statistical analysis plans that apply across all data types are discussed below. Data-type specific statistical analysis plans will be expanded upon in greater detail in subsequent pre-registrations for each data type. We intend to first analyze each data type separately (e.g., diffusion MRI data, cytokines, time use diaries), and then integrate them using machine learning approaches to identify multimodal changes associated with the intervention.

### Model assumptions and missing data

3.1

Prior to data analysis, model assumptions will be tested, including checks for normality, linearity, independence, multicollinearity, homoscedasticity, alongside extreme cases and outliers using techniques such as residual, Q-Q and scale-location plots, sample distribution, Cook's distance, and variance inflation factor (VIF). To ensure extreme cases do not drive effects, we will screen the data for outliers (e.g., using residuals, boxplots and histograms) and run models with and without these data points, confirming results with sensitivity checks, such as robust estimation where applicable. Where appropriate, we will use imputation to handle missing data.

### Model design

3.2

This study uses a longitudinal mixed-effects design with a hierarchical structure. Repeated measures data are nested within employees, who are nested within companies, meaning observations are not independent and will be analyzed using multilevel methods. The design includes one between-subjects factor (group: intervention and control) and one within-subjects factor (time, which will vary per analysis with three datapoint options: baseline and end of trial; baseline, end of trial and 6-month follow-up; and the weekly questionnaires), with an interaction between time and group and corrections for multiple tests. When relevant, employee-level (e.g., age, household income) and company-level (e.g., industry, company size) covariates will be added to statistical models. Table 1 provides a list of all planned covariates. The independent variables will be fixed effects, with up to three random effects: time, employee, and organization. Covariates will be added to the model as fixed effects. This design enables us to determine whether changes are observed across time points for the working time reduction intervention group but not for controls.

**Table 1 T1:** Planned individual-level and company-level covariates for inclusion in statistical models.

Category	Covariate	Type
Individual-level	Baseline value of dependent variable	Continuous
	Gender or sex	Categorical
	Household income	Categorical
	Education level	Categorical
	Age	Continuous
	Living area	Continuous
	Job title	Categorical
	Hours of working time reduction	Continuous
	Remote work status	Categorical
Company-level	Industry	Categorical
	Company size	Categorical
	Trial start month	Categorical
	Profit status	Categorical

The specific coding scheme used for categorical variables alongside any data specific covariates will be specified in future modality-specific preregistrations.

In line with other working time reduction trials, we will include all participants allocated to the intervention group in the primary analyses regardless of the actual extent of their working time reduction, unless the company average reduction of working hours is < 1 h per week. In which case, their data will be excluded from the main analyses. In secondary analyses, we will investigate whether intervention effects vary by the extent of working time reduction by adding this as a moderator in the mixed-effects models. The extent of working time reduction will be calculated as the difference between participants' self-reported weekly working hours before the trial and during the trial. Working time reduction will firstly be modeled as a continuous variable (hours reduced), but we will also explore potential non-linear relationships using categorical hourly brackets. Additional secondary analyses will investigate whether other individual characteristics moderate the intervention effects, such as sex, age, and baseline score for a given measure. Each potential moderator will be evaluated separately by including the relevant interaction terms in mixed-effects models.

Due to the range of data types and the number of variables, variable-specific hypotheses and model variations (i.e., specific moderators and additional covariates) will be addressed in multiple follow-up preregistrations on the Open Science Framework (OSF). These will provide further details on each data-type analysis within the OSF project repository.

